#### CaYou app

3.2.2

The CaYou app starts with a mandatory introductory module explaining its purpose, features, and content. This is followed by a 7-day EMA-learning phase, during which users receive five daily push notifications at random times. An AI-based reinforcement learning algorithm uses participants’ responses to notifications to identify optimal delivery times and locations. When participants confirm a prompt as well-timed, both the timestamp and GPS location, if allowed, are recorded. From week two to four, the system switch to a data-driven mode, delivering three EMAs per day based on previously identified optimal moments. Within a 4-h window between wake-up and bedtime, the algorithm monitors for suitable times or locations to trigger EMAs. If needed, prompts are delivered even without detected suitability to ensure appropriate spacing (minimum 4 h apart). Time and location feedback continues to refine the model throughout this phase. Following the fourth week, the algorithm is deactivated, and participants complete a final survey. While the AI individualize timing, the content is tailored to users’ mental well-being as assessed via daily EMA. The EMA includes the PHQ-4 (68) to monitor anxiety and depressive symptoms. If elevated symptoms are detected (PHQ-4 subscale score > 2), users receive targeted JITAI suggestions. Otherwise, they can select a topic of interest. JITAI exercises previously rated as helpful are saved as “favorites” and shown more frequently. Each JITAI is linked to an optional psychoeducative module.

The app content comprises one introductory module, two additional core modules to be completed at the start, and 15 optional topic-specific psychoeducative modules, each accompanied by a matching infocard that provides a concise overview. A final closing module focuses on reflection and relapse prevention after the 4-week intervention phase. All modules are delivered via an interactive chatbot that incorporates videos, audios, illustrations, fictional case examples from three personas illustrating challenges and solutions through speech bubbles, and interactive elements such as free-text and multiple-choice inputs. In addition, the app offers 67 JITAI exercises lasting between 2 and 15 min. These exercises are text- or audio-based, target specific goals (e.g., improving problem-solving skills), and provide practical, real-life strategies. Push notifications will be used daily to prompt users to complete EMA assessments and exercises, although all content is also freely accessible via a library within the app.

A central feature of CaYou is its dyadic component, which allows users to connect with a “Buddy”—such as a close friend or family member—who can provide support and motivation. Buddies can be linked through the app and view shared milestones like completed exercises, modules, or badges, thereby fostering interpersonal accountability and sustained engagement. Buddies do not access the app directly but receive automated email notifications when participants share achievements via standardized templates. A guide for the buddy will be created with study information and response templates for adherence alerts and participant achievements, designed to minimize mentor psychological burden while ensuring appropriate supportive communication.

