##### Data collection time points

3.2.4.1

Assessments will take place at screening (T0), baseline (T1), 10 days post-randomization (T2, only IG), and 4 weeks post-randomization (T3, post-intervention). Data collection includes online self-reports and telephone-based diagnostics (SCID-5). In-app assessments include daily EMA (PHQ-4) and repeated measures every 4 days (PHQ-4, TYDQ, CBTSQ [Things You Do Questionnaire and Cognitive-behavioral Therapy Skills Questionnaire]). In the IG, additional qualitative interviews after the app usage phase take place to explore their experiences with the study process, app usage, its acceptance, as well as facilitators and barriers to its application. Those who have discontinued the intervention will also be invited to identify barriers and reasons for dropout. An overview of all assessments and instruments is provided in Table 2.

**Table 2 tab2:** Assessment overview.

Instrument	Variable	Time of measurement					
		Screening	T0 Baseline	T1 10 Days	T2 Post	Daily	Course 4-days
Self-developed items	Inclusion criteria	x					
PHQ-ADS	Anxiety and depression	x					
BDI-II Item 9	Suicidal thoughts and behaviors	x			x		
PHQ-4	Anxiety and depression		x		x	x	x
Self-developed items	Sociodemographic data		x				
Self-developed items	Current medication		x		x		
ZUF-8	Treatment satisfaction			x	x		
Self-developed items				x	x		
TYDQ	Behaviors that promote mental health		x		x		x
INEP-On	Positive and negative effects of app use				x		
CBTSQ	CBT-Skills		x		x		x
SUS	Usability			x	x		
Self-developed items	Acceptability of data collection procedures				x		
Self-developed items	Concurrent treatment				x		
Self-developed items	Reasons for drop-out			x	x		
Diagnostic interviews							
SCID-5	Mental disorders, comorbidities, severity and chronicity		x				

PHQ-ADS, Patient Health Questionnaire Anxiety and Depression Scale; PHQ-4, Patient Health Questionnaire-4; BDI-2, Beck Depression Inventory-2; ZUF-8, Questionnaire for Patient Satisfaction 8; TYDQ, Things You Do Questionnaire; INEP-On, Inventory for Assessment of Negative Effects of Psychotherapy adapted to Online interventions; CBTSQ, Cognitive-Behavioral Therapy Skills Questionnaire; SUS, System Usability Scale; SCID-5, Structured Clinical Interview for DSM-5.

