1) Recruitment capability and resulting sample characteristics: Recruitment capability will be assessed by the number of individuals expressing interest in study participation, the intervention uptake rate, and the time required to reach the target sample. The traffic light system will evaluate whether the planned sample size (*N* = 60) is achieved within the 12-week recruitment period (see Table 3). Sample characteristics will be collected through sociodemographic data (e.g., age, gender, education, employment, relationship and parental status, residence size, nationality, ethnicity, migration status), family history of anxiety or depression, prior diagnoses, psychotherapy history, current medication or treatment, and experience with digital mental health tools.2) Data collection procedures and outcome measures: The appropriateness of data collection will be assessed through EMA and T2 data completeness, psychometric evaluation of outcome measures, and feedback from the study team. Participant perspectives on acceptability and appropriateness will be gathered at T2 using self-developed items and in the qualitative telephone interviews based on a custom interview guide (IG participants only).3) Acceptability and suitability of intervention and study procedures: Acceptability, satisfaction, and usability of the app will be measured using the German version (ZUF-8; *α* = 0.90, 8 items, score range: 8–32) of the Client Satisfaction Questionnaire (CSQ) (71), the System Usability Scale (SUS; *α* = 0.91, 10 items, score range: 0–40) (72), and self-developed items. At T2, qualitative telephone interviews will further explore participants’ experiences with the app’s features, content, and overall impressions. Intervention adherence will be measured via user engagement metrics (e.g., number of modules and exercises completed, usage days during the 4-week period, buddy interactions, and optional sensor data). Reasons for dropout will be assessed through self-developed items and within the qualitative interview at T2.4) Resources and ability to manage and implement the study and intervention: The study team will document time and personnel resources needed for app development, study administration, and participant support.5) Participant responses to the intervention: Symptoms of anxiety and depression will be measured using the Patient Health Questionnaire Anxiety and Depression Scale (PHQ-ADS; *α* = 0.88–0.92, 16 items; score range: 0–48) (73), which combines the Patient Health Questionnaire 9 (PHQ-9; *α* = 0.89, 9 items, score range: 0–27) (51, 74) and the Generalized Anxiety Disorder Scale 7 (GAD-7; *α* = 0.89, 7 items, score range: 0–21) (75). The PHQ-ADS has shown high internal consistency (*α* = 0.88–0.92). Cognitive behavioral skills will be measured using the Cognitive-behavioral Therapy Skills Questionnaire (CBTSQ; *α* = 0.90, 16 items, score range 16–80), covering behavioral activation (*α* = 0.85) and cognitive restructuring (*α* = 0.88) (76). The Things You Do Questionnaire (TYDQ; *α* = 0.90, 15 items, score range: 0–60) (77) will assess engagement in positive routines and meaningful activities, with higher scores indicating greater engagement (*α* = 0.90). Qualitative interviews at T2 will explore the perceived effects of the app from the IG participants’ perspective.6) Risks and negative events: The benefit–risk ratio will be assessed by tracking adverse events, including reliable symptom improvement and deterioration according to the reliable change index (RCI) by Jacobson and Truax for the PHQ-ADS, indicating a decrease or increase of >1.96 from T1 to T3 as well as suicidal thoughts and behaviors (78). These will be measured at T2 using the INEP-On (Inventory for Assessment of Negative Effects of Psychotherapy adapted to online interventions; *α* = 0.86, 21 items) (79), item 9 of the PHQ-ADS (73), and item 9 from the BDI-II (80). Qualitative interviews will further explore perceived negative effects of the app.

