
**Table 3 tab3:** Traffic light system for assessing feasibility.

Traffic light system for assessing feasibility	Green	Yellow	Red
1. Participants recruited during the planned period (%)	*N* = 60 (100%)	*N* = 45–59 (75–98%)	*N* < 45 (<75%)
2. Participants with complete data at post-assessment (percentage of the total sample)	>70%	50–70%	<50%
3. Completed EMA data (at least one EMA completed per day; percentage of the total sample)	>60%	40–60%	<40%
4. Omega value for two-thirds of the outcome questionnaires	≥0.70	0.60–0.69	<0.59
5. Satisfaction (ZUF-8)	*M* > 26	*M* = 24–26	*M* < 24
6. Pre-post change in the PHQ-4 scores compared to the control group (depression and anxiety subscales)	Baseline score ≤3: No reliable deterioration, indeterminate, or reliable improvement Baseline score > 3: No deterioration or improvement reliable to deterioration and improvement	No improvement reliable to improvement in participants with a baseline score > 3	Symptom deterioration reliable to deterioration
7. Risk–benefit ratio	Positive	Negative: Isolated negative intervention-related events, that can be addressed by revising the intervention or study	Negative: Serious adverse intervention-related events (e.g., suicidal thoughts), symptom deterioration

EMA, Ecological Momentary Assessment; ZUF-8, Questionnaire for Patient Satisfaction 8.

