#### Safety concept

3.2.6

Data on adverse and serious adverse events will be collected at different assessment points throughout stage II as recommended (81). Suicidal thoughts and behaviors will be assessed with PHQ-ADS item 9 (73) and BDI-II item 9 (80) at screening, and INEP-On item 20 at T2. Other negative events will be assessed with the INEP-On at T2. Relevant indications may also emerge from participants’ responses during the screening or qualitative post-intervention interview.

A detailed safety protocol, based on existing recommendations (77) outlines procedures for managing negative events. These include automated provision of help resources via questionnaires and email, and individual therapeutic phone consultations following a structured emergency plan tailored to the severity of suicidal ideation. A licensed psychotherapist will be available for consultations, and screening interviewers will be trained and supervised in implementing the emergency plan. All adverse events will be documented.

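### Symptom deterioration is defined only by change to the post-assessment, so intervention participants without one have no deterioration status, although in-app PHQ-4 scores may exist for them

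*Protocol article*

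**What the plan says.** **Deterioration as a harm.** Section 3.2.4.2 (Feasibility measures), item 6, counts reliable change on the PHQ-ADS among the tracked adverse events, "indicating a decrease or increase of >1.96 from T1 to T3 as well as suicidal thoughts and behaviors". Table 3, row 7, gives as its red entry "Serious adverse intervention-related events (e.g., suicidal thoughts), symptom deterioration". Table 3, row 6, rates "Pre-post change in the PHQ-4 scores compared to the control group (depression and anxiety subscales").

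**Safety sources.** Section 3.2.6 (Safety concept) opens with "Data on adverse and serious adverse events will be collected at different assessment points throughout stage II as recommended (81"). It then names PHQ-ADS item 9 and BDI-II item 9 at screening and INEP-On item 20 at T2. It adds "Other negative events will be assessed with the INEP-On at T2" and "Relevant indications may also emerge from participants’ responses during the screening or qualitative post-intervention interview". It also refers to a detailed safety protocol, which is not shown.

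**In-app data.** Section 3.2.4.1 (Data collection time points) states: "In-app assessments include daily EMA (PHQ-4) and repeated measures every 4 days", the latter including PHQ-4, TYDQ and CBTSQ. Section 3.2.2 (CaYou app) gives one consequence of a raised score: "If elevated symptoms are detected (PHQ-4 subscale score > 2), users receive targeted JITAI suggestions". Section 3.2.5.1 sends the 4-day series to exploratory time-series analyses.

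**Schedule.** Table 2 places PHQ-ADS at screening only, PHQ-4 at baseline and post, and INEP-On at post only. Its 10-day column holds satisfaction, usability, self-developed and drop-out items, with no symptom or harm scale.

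**The concern.** Risks and adverse effects are one of the six questions this study is meant to answer (section 2, Aims), and deterioration is a red trigger. A person can be classed as deteriorated only if a post value exists. Those who worsen may well be the ones who do not return for it. If so, a risk–benefit rating built on completers looks better than the truth, in a trial small enough for one or two cases to matter.

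The intervention arm is asked for symptom scores throughout the four weeks. Some of those lost before post-assessment will have PHQ-4 values up to their last use of the app, and no stated deterioration rule uses them. The Safety concept describes collection across the whole stage, but the sources it lists sit at screening and, on Table 2's labels, at post.

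**Working it through.** The protocol states no figure for this point, so there is nothing to reproduce. The check compares the passages and then sizes the gap.

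**1. Which value each rule needs**

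| Rule | Where | Needs | Scheduled in Table 2? |
|---|---|---|---|
| Reliable change, PHQ-ADS, T1 to T3 | 3.2.4.2, item 6 | PHQ-ADS at both ends | No: screening only |
| Pre-post PHQ-4 against control | Table 3, row 6 | PHQ-4 at baseline and post | Yes |
| Symptom deterioration | Table 3, row 7 | Not stated in the row | – |

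Row 7 gives no rule of its own, so it has to borrow one of the first two, and both need a post value. The first cannot be computed from Table 2 for anyone. Item 6 also says PHQ-ADS item 9 is measured at T2, which Table 2 does not show. PHQ-4 is therefore the only symptom scale that Table 2 repeats after baseline.

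**2. What T2 means.** Figure 1's legend and the text of section 3.2.4.1 make T2 the 10-day point (intervention arm only) and T3 the post-assessment. Table 2 labels the 10-day point T1 and the post-assessment T2. The deterioration rule uses the first labelling. INEP-On at T2 agrees with Table 2 only under the second.

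**3. In-app data requested per intervention participant**
- Daily prompts: 7 days × 5 + 21 days × 3 = 98.
- Four-day measures: 28 / 4 = 7.

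These are prompts sent, not answers received. The waitlist arm has no app during the comparison.

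**4. Participants without a deterioration status**
- Planned dropout (section 3.2.3): 0.20 × 30 = 6 per arm; 0.20 × 60 = 12 in total.
- Table 3, row 2, green (more than 70% complete): at least 43 of 60, so up to 60 − 43 = 17 missing.
- Table 3, row 2, yellow (50–70% complete): at least 30 of 60, so up to 30 missing. Section 3.2.5.1 still calls this feasible. Split equally, that is 15 per arm.

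**5. Chance of at least one unclassified case.** For n intervention dropouts who each deteriorate with probability p, the expected number is n × p and the chance of at least one is 1 − (1 − p)^n. The documents give no value for p, so a range is shown.

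| p (assumed) | n = 6: expected | n = 6: at least one | n = 15: at least one |
|---|---|---|---|
| 5% | 0.3 | 26% | 54% |
| 10% | 0.6 | 47% | 79% |
| 20% | 1.2 | 74% | 96% |
| 30% | 1.8 | 88% | over 99% |

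Example: 1 − 0.90^6 = 1 − 0.531 = 0.469.

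**6. Direction.** If dropouts and completers deteriorate at the same rate, the completer proportion is not biased, though the count is short. The rating leans towards positive only if those who worsen are lost more often. That is plausible, but it is an assumption.

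**The case against.** The strongest reply is that this is a condensed article. It says a detailed safety protocol exists, with automated help resources, a structured emergency plan and a licensed psychotherapist available. Handling of missing post values is also commonly left to an analysis plan. This stands as far as action on scores is concerned. A reader might infer that nobody is assigned to act on the in-app scores, but the text does not support that, because the safety protocol is not shown and may cover them.

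A reader might also infer that worsening in dropouts is never counted. That goes too far. Participants who discontinue are invited to interviews, the interviews explore perceived negative effects, and the 4-day series can enter the exploratory trajectories. None of these is described as a systematic count of deterioration, but each can bring a case to light. An event reported by a dropout could also count in row 7, which states no pre-post rule.

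Two further limits stand. Stopping the app is not the same as missing the post-assessment: someone who stops in week 2 and completes the online post survey is classed normally. And in-app data exist in one arm only and end with app use, so they cannot serve the between-group comparison in row 6.

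The reply does not remove what the article itself fixes: deterioration rules that need a post value, a list of safety sources without the in-app PHQ-4, and a schedule in which the PHQ-ADS rule cannot be computed.

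**Conclusion.** The point holds in a limited form. As printed, intervention participants without a post-assessment cannot be classed as deteriorated under either stated rule, although PHQ-4 values up to their last app use may exist. That is about 6 of 30 at the planned dropout, and up to about 15 within the completeness band still rated yellow if losses split equally. The effect on the risk–benefit rating is towards positive if those who worsen are lost more often; its size cannot be derived from the documents. Any specific contrast between a completer rate and a true rate would rest on an invented split of cases. The 47–88% range rests on 6 dropouts, independent outcomes and an assumed deterioration rate of 10–30%.

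The schedule problem is separate and affects completers too: Table 2 has no PHQ-ADS at either end of the T1-to-T3 interval, and T2 has two meanings. Neither the study's design nor its sample needs to change, but the harm rating should not rest on completers alone when relevant data are already being collected.

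**What to change.** 1. **Supplementary count for Table 3, row 7.** For intervention participants without a post value, compare the last available 4-day in-app PHQ-4 (or, failing that, the last daily one) with baseline PHQ-4, using the same reliable-change rule as row 6. Report the number beside the completer result, with the number who have no in-app value either. Label it descriptive and keep it out of the row 6 comparison.

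2. **Reconcile the passages.** Bring the statement in section 3.2.6 about collection across the stage into line with the sources listed there and with section 3.2.2. State whether the existing safety protocol covers in-app PHQ-4. Use one set of time-point labels in the text, Figure 1 and Table 2. Make the PHQ-ADS schedule in Table 2 agree with the T1-to-T3 rule in section 3.2.4.2. Any action level or pathway for raised scores is for the clinical team.

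**Cost.** The count needs protocol wording and an export of data already collected. Correcting the PHQ-ADS schedule is an edit to Table 2 if the scale is already given at those points; otherwise either the rule or the assessments must change. The count has limits: it covers one arm, its data end with app use, a single last value is noisy, and the article does not say whether in-app and baseline PHQ-4 share a recall period.

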#### Sample size and power calculation

3.2.3

For stage II, the sample size was calculated following pilot study guidelines (69). To detect a very small effect (*d* < 0.3) on the PHQ-4 at post-assessment (*α* = 0.05, *β* = 80%), and accounting for an anticipated 20% dropout rate, *n* = 30 participants per group are required, yielding a total sample size of *N* = 60 participants.

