## Aims

2

This study aims to develop and test a dyadic, AI-driven Just-In-Time Adaptive Intervention app (DyAI-JITAI) for the prevention of anxiety and depressive disorders in a non-clinical adult population. It comprises two consecutive stages. In stage I, a participatory design approach was used to co-develop the app with potential users. Through iterative qualitative methods, we identified and adapted intervention content and features based on expectations, experiences, needs, and preferences of the target group. Stage II involves a two-arm randomized controlled proof-of-concept study to assess the feasibility, acceptability, and preliminary clinical relevance of the DyAI-JITAI and the feasibility of a subsequent randomized controlled clinical trial. Specifically, we will evaluate (1) recruitment and sample characteristics, (2) data collection and outcome measures, (3) acceptability and satisfaction, (4) resource requirements, (5) user engagement and preliminary efficacy, and (6) potential risks and adverse effects. We hypothesize that the DyAI-JITAI app will be usable, acceptable, and effective in supporting CBT skill acquisition and behavioral change in daily life.

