##### Randomization

3.2.1.3

Eligible individuals will be randomly allocated to the IG or WLC by an independent researcher using block randomization (blocks of 4 and 6 to minimize predictability in allocation) via Sealed Envelope.^1^ Participants will be informed of their group allocation; those in the IG will receive immediate access to the CaYou app, while WLC participants will gain access after 4 weeks.

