##### Quantitative data analysis

3.2.5.1

The intervention is considered feasible if all criteria in the traffic light system are rated yellow or green (see Table 3). Yellow ratings will prompt internal discussion and minor adjustments; red ratings indicate the need for major revisions, with input from external experts. Quantitative baseline data will be analyzed descriptively. Mental health outcomes will be examined using analysis of covariance (ANCOVA) to assess between-group pre-post changes, and time series analyses will explore individual symptom trajectories based on 4-day intervals.

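### The sample-size statement is wrong as written: 30 per group with 20% dropout gives about 17% power (22–30% with ANCOVA), not 80%, for d = 0.3 on the PHQ-4

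*Protocol article*

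**What the plan says.** Section 3.2.3 (Sample size and power calculation) opens by saying that the Stage II size follows pilot study guidelines, citing a source. It then gives a complete power statement:

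- Target: "To detect a very small effect (*d* < 0.3) on the PHQ-4 at post-assessment".
- Error rates: "α* = 0.05, *β* = 80" per cent.
- Attrition: "accounting for an anticipated 20% dropout rate".
- Result: "n* = 30 participants per group are required", "yielding a total sample size of *N* = 60 participants".

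Section 3.2.5.1 (Quantitative data analysis) names the analysis: "Mental health outcomes will be examined using analysis of covariance (ANCOVA) to assess between-group pre-post changes". The same section makes the feasibility decision depend on the traffic-light criteria in Table 3. Section 2 (Aims) lists preliminary efficacy among the things to be evaluated.

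**The concern.** The section names an effect size, an alpha, a power, a dropout rate and a resulting n, so the calculation can be checked. Detecting a standardised difference of 0.3 between two groups with 80% power normally takes well over a hundred participants per arm, and 30 is far from that. Two further features of the sentence are wrong in themselves. An effect given only as below 0.3 is an open range, from which no single n follows. A β of 80% means, literally, 20% power.

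At stake is what a reader believes the PHQ-4 comparison can show. Someone told that the trial has 80% power for effects below 0.3 could take a null result as evidence against even a small effect. The design would in fact miss a true d = 0.3 most of the time.

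**Working it through.** **Inputs.** From section 3.2.3: d = 0.3 (upper edge of the stated range), alpha 0.05, power 80%, dropout 20%, 30 per group. Allocation is taken as 1:1, from the equal group sizes and from "using block randomization (blocks of 4 and 6 to minimize predictability in allocation"). Sidedness is not stated, so two-sided is assumed and one-sided is also tried. The baseline–post correlation r is not stated, so a range is shown.

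**Step 1. Number analysed.** 30 × (1 − 0.20) = 24 per arm.

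**Step 2. Try to reproduce the plan's 30.**
n per arm = 2(z₀.₉₇₅ + z₀.₈₀)² / d² = 2(1.960 + 0.842)² / 0.09 ≈ 174.4, so 175. The t-based solution is 175.4, so 176. After dropout: 176 / 0.80 = 220 per arm, 440 in total. This is about seven times the stated 30 (220 / 30 = 7.3).

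Other readings, all at d = 0.3 unless stated (normal approximation, except the paired and F tests):

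| Reading | Completers | After dropout |
|---|---|---|
| One-sided alpha 0.05 | 138 per arm | 173 per arm |
| β literally 80% (20% power) | 28 per arm | 35 per arm |
| ANCOVA, r = 0.5 | 131 per arm | 164 per arm |
| ANCOVA, r = 0.7 | 89 per arm | 112 per arm |
| Paired within-group test | about 90 in one group | – |
| Cohen's f = 0.3 (d = 0.6) | 44 per arm | 55 per arm |

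A repeated-measures group-by-time test with f = 0.15, seven measurements and within-person correlation 0.5 needs N = 46 in total, or 58 with dropout, which is close to 60. It is a different target. If the groups diverge linearly to a final difference D over seven occasions, f = ½ · D · (2/6) = D/6, so f = 0.15 means D = 0.9 at post-assessment, not a value below 0.3. No reading that matches the stated inputs gives 30.

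**Step 3. Power of the stated design, unadjusted.**
Normal approximation: Φ(d√(n/2) − 1.960) = Φ(0.3 × √12 − 1.960) = Φ(1.039 − 1.960) = Φ(−0.921) ≈ 17.9%. The noncentral t gives 17.4%.

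- No dropout (30 per arm): 20.8%.
- One-sided, 24 per arm: 26.7%.
- Smaller effects inside the stated range, 24 per arm, two-sided: 10.4% at d = 0.2 and 6.3% at d = 0.1.

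**Step 4. Power with the planned ANCOVA.** Replace d by d/√(1 − r²), 24 per arm, two-sided, noncentral t:

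| Assumed r | 0.3 | 0.5 | 0.7 | 0.8 | 0.9 |
|---|---|---|---|---|---|
| Power at d = 0.3 | 19% | 22% | 30% | 40% | 65% |

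Reaching 80% would need r of about 0.93.

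**Step 5. What 24 per arm can detect at 80% power.** Unadjusted (t): d ≈ 0.83. Multiply by √(1 − r²): 0.826 × 0.866 ≈ 0.72 at r = 0.5, and 0.826 × 0.714 ≈ 0.59 at r = 0.7.

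**Step 6. Precision.** 95% CI half-width for the standardised difference, taken at d = 0.3: 1.96 × √(2/24 + 0.09/96) = 1.96 × 0.290 ≈ 0.57 SD unadjusted. With ANCOVA: 0.57 × 0.866 ≈ 0.49 SD at r = 0.5, and 0.57 × 0.714 ≈ 0.41 SD at r = 0.7.

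**The case against.** The best defence is that this is a pilot. The section's first sentence names pilot guidelines as the basis, and an effect given as a range looks more like an effect-size category than a design value. The d, alpha and power may therefore describe a later main trial, with 30 per arm taken from a pilot rule and the two run together in a condensed article. The cited source is not available, so this cannot be settled. It does not rescue the sentence, which says that 30 per group are what detecting the effect requires. If the figures belong to a future trial, the text must say so. What stands is that 30 per arm may well suit the feasibility aims, and nothing here argues for a larger trial.

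It is also fair that 17% is not the power of the planned analysis. ANCOVA does better, and 22–30% is the relevant range at the assumed correlations. That is still far below 80%.

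Two stronger readings are tempting but unsupported:

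- A reader might infer that a non-significant, or chance-significant, ANCOVA would mislead the decision on the full trial. Under section 3.2.5.1 feasibility depends on the traffic-light criteria, and none of the seven in Table 3 is an ANCOVA p-value. The criterion on PHQ-4 change against control is defined by reliable change. The ANCOVA carries no stated decision rule.
- A reader might infer that the trial's efficacy hypothesis rests on this underpowered PHQ-4 test. The hypothesis in Section 2 reads "We hypothesize that the DyAI-JITAI app will be usable, acceptable, and effective in supporting CBT skill acquisition and behavioral change in daily life". It concerns skills and behaviour, and the clinical claims around it are expressly preliminary.

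**Conclusion.** The sample-size statement is wrong as written and should be corrected. At the most favourable edge of its stated range the design has about 17% two-sided power unadjusted, against the 80% claimed, and even an assumed r of 0.9 does not reach 80%. The conclusion rests on three assumptions: 1:1 allocation, 24 analysed per arm, and β of 80% meant as power of 80%. It does not depend on sidedness, on whether dropout is counted, or on any plausible baseline correlation.

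The consequence is limited to a false statement of sensitivity for the preliminary-efficacy comparison. Misreading of a null result is a reasonable worry about readers, not something the plan commits to.

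**What to change.** Keep N = 60 and rewrite section 3.2.3:

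1. Delete the claim that 30 per group give 80% power for d below 0.3. If those figures were meant for the future trial, say so and separate them from the justification of N = 60.
2. Justify 30 per arm as a pilot size, for estimating feasibility rates and the outcome SD.
3. State the real sensitivity: with about 24 analysed per arm, 80% power exists only for d of about 0.83 unadjusted, or about 0.72 / 0.59 with ANCOVA at assumed r = 0.5 / 0.7.
4. State the precision: a 95% CI half-width of about 0.57 SD unadjusted, or about 0.49 / 0.41 SD adjusted at the same correlations. The adjusted figures are the ones that match the planned analysis.
5. Wherever a power figure is kept, write power = 80% in place of β, and give a single effect size and the sidedness.
6. In section 3.2.5.1, describe the PHQ-4 ANCOVA as exploratory, reported as an adjusted difference with a 95% CI.

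The cost is rewording only, with no extra participants and no change to design or decision rule. The one downside is that the stated sensitivity becomes less favourable.
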